### 10.3.4 STATISTICAL ANALYSIS OF THE SECONDARY END POINTS

For **binary secondary endpoints** (such as rejection) absolute ( $n=x$ ) and frequencies in percentage (%) will be calculated per treatment group. 95%-confidence intervals will be calculated for rates, if appropriate. Such data will be visualized with bar charts. If appropriate, logistic regression models will be applied using treatment as independent factor. Furthermore, the model will be adjusted for sex and age.

For **time-to-event endpoints** (such as overall survival) Kaplan-Meier plots will be provided. The two-group will be compared with log-rank tests. Additionally Cox-Regressions models will be performed adjusting for additional factors as described for the primary analysis.

For recurrent events (such as infections) the appropriate survival methods will be applied. This includes the Negative Binomial Regression models, Anderson and Gill models and Frailty models. Hazard ratios and corresponding two-sided 95% confidence intervals will be reported.

**Continuous secondary endpoints** such as laboratory values or "SF36" will be summarized by mean, standard deviation, median, first and third quartiles, minimum and maximum for each treatment arm separately. If a continuous endpoint is measured only at one time point after randomization, it will be analysed using an analysis of covariance using the factor treatment group adjusting for the factors sex and the covariate age (in years). Mean estimates will be provided, together with their corresponding two-sided 95% confidence intervals. If repeated measurements are available for several visits after randomisation, a mixed model for repeated measurements will be performed using patient as random factor and treatment arm as fixed

factor. If baseline values are collected, they will be included as covariate in the analysis of covariance and mixed model for repeated measurements.

#### 10.3.5 MULTIPLE TESTING

For the primary endpoint we will use a hierarchical testing procedure. This means first we will test the non-inferiority hypothesis at a one-sided alpha of 2.5%. After non-inferiority can be demonstrated, superiority will be tested also using a one-sided alpha of 2.5%.

The secondary endpoints include the components of the primary outcome and are needed to support the interpretation of the potential effects in the primary endpoint. The tests for this comparisons would require larger sample sizes to achieve the required power. This was the reason why a composite endpoint has been chosen and these analyses are considered supportive only without further multiplicity correction.

For the analyses of all secondary endpoints two-sided p-values and two-sided 95%-confidence intervals will be reported.

#### 10.3.6 INTERIM ANALYSIS

There will be no interim analysis for efficacy. The DSMB will monitor the trial for safety purposes.

#### 10.3.7 MISSING VALUES

For the primary analysis missing values will be considered as treatment failures in the composite primary endpoint. Additionally meaningful missing values will be imputed by statistical models for the data according to underlining mechanism of missing data. Sensitivity analyses will be performed for imputed data.

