### 10.2 SAMPLE SIZE CALCULATION

For the sample size calculation, we analysed the occurrence of the primary endpoint (infection, allograft rejection, death and graft loss) in recipients of a kidney allograft transplanted between 1.1.2012 and 31.12.2018 at the Vienna centre, applying the trial-specific inclusion and exclusion criteria (unpublished data). Overall, 40% of patients experienced the primary endpoint between month 3 and 12 after transplantation. Therefore, we assume a composite rate of around 40% in the standard dosing (arm S).

It is expected that the TTV-guided immunosuppression (arm T) reduces the occurrence of the primary endpoint, and therefore rates between 20% and 30% are assumed to be reasonable.

The non-inferiority margin has been fixed 10% points (see also above). Thus when the sample size in each group is 120, a two-group large-sample normal approximation test of proportions with a one-sided 2.5% significance level will have 90.42% power to reject the null hypothesis

that arm T is inferior to standard arm S (the difference in proportions,  $\pi_1 - \pi_0$ , is 0.1 or farther from zero in the same direction) in favour of the alternative hypothesis arm T is not inferior to arm S, assuming that the expected proportions are 0.3 and 0.4 in arm T and S, respectively (i.e. assuming a better outcome in arm T).

Due to the planned observation period of 9 months and the special patient population, a rather low drop-out rate is expected of about 2-5%. Adjusting for potential drop-outs, the sample size is fixed with 130 patients per group, i.e., 260 in total.

The sample size calculation was performed using N-Query Version 8.6.1.

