### 10.3.3 STATISTICAL ANALYSIS OF THE PRIMARY END POINT

The occurrence of the primary composite endpoint will be presented per treatment group as absolute numbers and percentages. The difference of the occurrence of the primary endpoint between the two treatment groups and a two-sided 95% confidence interval will be calculated.

Non-inferiority will be concluded if the upper limit of a two-sided 95% confidence interval for the difference in proportion of patients at month 9 after randomization (= Visit 7; post-transplant month 12) between the two treatment arms is less than 10% points. Superiority will be concluded if the confidence interval excludes 0.

As additional sensitivity analyses confidence intervals will be calculated being adjusted for study stratifications (such as centers) using Cochrane-Mantel-Haenszel weights. Also logistic regression models will be used using additional factors (such as sex) and covariate (such as age at randomization).

To explore the composite endpoint further, it will be also be analyzed as time-to-event endpoint considering the time from randomization till time of first event. We will visualize these data by presenting Kaplan-Meier curves for each treatment arm. Furthermore, Cox-regressions models will be performed adjusting for the same factors and covariates as used in the logistic regression models.

To address the repetitive nature of the events used in the definition of the primary endpoint, we will also perform supportive analyses for recurrent event data. We will fit a negative Binomial regression model for the events of the composite endpoints accounting for the time a patient is under risk. Furthermore, we will perform the counting process model of Andersen-Gill and frailty models.

To assess the impact of the individual components of the composite endpoints, each component will be analyzed descriptively (see description for secondary endpoints).

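### Counting missing outcomes as failures in both arms makes the primary non-inferiority test mildly anti-conservative when missingness is similar in the two arms and unrelated to outcome

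*Protocol*

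**What the plan says.** Protocol section 10.3.7 sets the handling for the primary test: "For the primary analysis missing values will be considered as treatment failures in the composite primary endpoint". It makes no distinction by arm. Model-based imputation comes in addition: "Sensitivity analyses will be performed for imputed data".

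The test it feeds is defined in three places. Section 10.3.3: "Non-inferiority will be concluded if the upper limit of a two-sided 95% confidence interval for the difference in proportion of patients" is below 10 points. Section 10.2: "The non-inferiority margin has been fixed 10% points". Section 10.3.5: "first we will test the non-inferiority hypothesis at a one-sided alpha of 2.5" percent.

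On the amount of missing data, section 10.2 says "a rather low drop-out rate is expected of about 2-5" percent, with no split by arm. Section 3.2 builds the composite from infection, rejection, death and graft loss. Withdrawal and missing outcome are not components.

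**The concern.** Treating missing as failure is often thought cautious. That intuition comes from superiority trials, where pulling two arms together works against the claim. In a non-inferiority trial it works for the claim: adding the same share of failures to both arms narrows the gap that the test is meant to detect.

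The main conclusion of the trial rests on this analysis. The null hypothesis in section 10.1 is a true excess of 10 points or more in the TTV-guided arm. If the analysed difference at that boundary is below 10 points, the test no longer has its stated level for the endpoint in section 3.2. The rule could be defended if withdrawal were meant to be an event, but section 3.2 does not define it so.

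**Working it through.** **Inputs.** From the protocol: 10-point margin, one-sided 2.5%, rates 0.30 (T) and 0.40 (S), 120 evaluable and 130 randomised per arm, 2–5% dropout. Assumed: the boundary case of 0.50 (T) against 0.40 (S), which is the planned control rate plus the margin; missingness independent of outcome within each arm; all missing shares by arm.

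**Reproducing the plan's figure.** The probability of concluding non-inferiority is Φ((0.10 − (pT − pS))/SE − 1.96), with SE = √(pT(1−pT)/n + pS(1−pS)/n). At n = 120, SE = √(0.45/120) = 0.0612, and Φ(0.20/0.0612 − 1.96) = 90.42%. Section 10.2 says the test "will have 90.42% power to reject the null hypothesis", so the method matches.

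**Effect of the rule.** With share m missing, the analysed rate is p(1 − m) + m. At the boundary:

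- T: 0.50 + 0.5·mT
- S: 0.40 + 0.6·mS
- difference: 0.10 + 0.5·mT − 0.6·mS

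With mT = mS = m this is 0.10·(1 − m). The difference falls below 0.10, and the error above 2.5%, only when mT < 1.2·mS.

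**Two cases in full** (n = 130 per arm):

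- 5% missing in each arm: rates 0.525 and 0.430, difference 0.095, SE = √((0.2494 + 0.2451)/130) = 0.0617. Error = Φ(0.005/0.0617 − 1.96) = Φ(−1.88) = 3.0%.
- 2% in T, 5% in S: rates 0.510 and 0.430, difference 0.080, SE = 0.0617. Error = Φ(0.020/0.0617 − 1.96) = Φ(−1.64) = 5.1%.

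**Results**, with exact binomial enumeration of the simple Wald interval alongside:

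| Missing T | Missing S | Analysed difference (points) | Error, approximation | Error, exact |
|---|---|---|---|---|
| 0% | 0% | 10.0 | 2.50% | 2.63% |
| 2% | 2% | 9.8 | 2.70% | 2.86% |
| 5% | 5% | 9.5 | 3.01% | 3.22% |
| 2% | 5% | 8.0 | 5.1% | 5.4% |
| 5% | 2% | 11.3 | 1.5% | 1.6% |
| 6% | 5% | 10.0 | 2.5% | 2.7% |

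With a control rate of 30% or 50%, the approximation again gives 2.7% at 2% and 3.0% at 5% missing per arm.

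**Other consequences.** The later superiority test is not inflated under equal missingness (2.5% at 0, 2 and 5% missing). Power at 30% against 40% under the rule is 91.6% at 2% missing and 90.2% at 5%. With complete cases it would be 91.9% (127 per arm) and 91.3% (124 per arm), with the error at 2.5% by the same approximation.

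**The case against.** A reader might infer that the 2.5% level is exceeded whatever happens. The documents do not support that. The excess needs mT < 1.2·mS, and with clearly more missing in the TTV-guided arm the rule is conservative. It also needs missingness unrelated to outcome. If patients lost from both arms share one event risk q, the counted rate is p + m(1 − q) in each arm, and with equal m the 10-point difference is preserved.

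A reader might also infer that, because investigators know the allocation, losses will pile up in the control arm. Nothing in the protocol shows this. Participants are blinded (5.11.1). Visits continue after trial therapy stops (6.21). A final visit is sought from those who withdraw (6.22), and calls are made every two weeks (6.13). Patients with an event before leaving are already failures. Outcomes truly missing may therefore be fewer than dropouts.

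The plan has partial cover as well: imputation in 10.3.7, time-to-event analyses in 10.3.3, further analysis sets in 10.3.1, and more detail deferred to the SAP. And the alternatives are not free of bias: censoring can hide harm-related dropout in arm T, which missing-as-failure would count.

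Most of this stands and limits the size and certainty of the point. It does not remove it. The imputation and the time-to-event analyses are sensitivity or supportive analyses, and the other analysis sets change who is analysed, not how a missing outcome counts. The rule for the primary test is fixed in the protocol, so it is not a detail left to the SAP.

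**Conclusion.** The point holds in a limited form. With similar, outcome-independent missingness in both arms, the natural planning case, the primary rule tilts the test towards the non-inferiority claim. At the protocol's own 2–5% dropout the tilt is small: about 2.7–3.0% instead of 2.5% (exact 2.9–3.2%, against 2.6% with nothing missing).

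The larger figure of 5.1% rests on an assumed imbalance of 2% in T and 5% in S. The mirror image gives 1.5%. Since no split by arm is given, neither should be read as a prediction. They show that the level of the primary test depends on how losses happen to divide. This is a modest flaw in the main analysis, worth correcting because the correction is cheap. It does not make the design unsound.

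**What to change.** Amend sections 10.3.3 and 10.3.7, and the SAP to match:

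- **Primary estimate.** Use one that does not dilute the difference: either multiple imputation under missing-at-random using follow-up to last contact, or the difference in Kaplan-Meier risk at a named day after randomisation (Visit 7 has a ±14-day window). Death and graft loss are in the composite, so neither is a competing event.
- **Sensitivity.** Keep missing-as-failure in both arms here.
- **Adverse case.** Pre-specify one analysis that works against the claim: missing in T counted as an event and missing in S as no event, or a tipping-point analysis.

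The cost is wording. No patients are added, Kaplan-Meier curves are already planned, and the two-weekly calls help to date last contact. The downside is that the new primary analysis assumes missing-at-random or non-informative censoring, which could hide dropout caused by harm in arm T. The adverse-case analysis is there to expose that.

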#### 10.3.8 EXPLORATORY SUBGROUP ANALYSIS

Subgroup analysis will be performed in patients at risk for immunological (re-transplantation) and infectious (diabetes mellitus) events and according to age group (>55 years of age), gender and study centre. If appropriate this factors will be included as additional covariates in the regression models as described above.

#### 10.3.9 STATISTICAL SOFTWARE

All statistical analyses will be conducted with statistical software like SAS 9.4. (or higher), R 3.6.3. (or higher) or IBM SPSS Statistics (SPSS Inc., Chicago, IL, USA), STATA (StataCorp, College Station, TX, USA), MS EXCEL (Microsoft, USA). Any deviation from the original statistical plan will be described and justified in the protocol and in the final report.

## 11 ETHICAL, LEGAL AND ADMINISTRATIVE ASPECTS

### 11.1 RESPONSIBILITIES OF SPONSOR AND INVESTIGATOR

The sponsor of the clinical trial (Medical University of Vienna) assumes responsibility for the initiation, organization and funding of the clinical trial to be conducted in accordance to national laws. To this end, the clinical trial must be registered in the EudraCT database before the application for approval by the Member states concerned.

The sponsor and the investigator ensure that the clinical trial is conducted in accordance with existing laws and regulations, in accordance with the ICH-GCP guidelines, the Declaration of Helsinki (2013), the Regulation (EU) No 536/2014 as well as the provisions of the national laws.

The investigator accepts the requirements of the signed trial protocol.

His or her responsibilities include:

- understanding the characteristics of the IMP described in the Investigator's Brochure or the Summary of Product Characteristics,
- understanding and implementing the treatment plan,
- ensure that sufficient time and capacity are available to conduct the trial,
- correct collection and documentation of data, reporting,
- provision of all data for sponsor, monitoring or corresponding authorities for audits and/ or inspections,
- ensure that the information on trial subjects and all information received from the sponsor is kept confidential by all persons involved in the trial,
- statement on the involvement of persons possibly dependent on the sponsor or the investigator,
- information on possible economic and other interests of the investigators in connection with the IMP.

According to EU regulation No 536/2014, the respective investigator assumes responsibility for conducting the clinical trial at the trial site.

We confirm that the proposed trial will comply with established ethical principles, EU regulation No 536/2014 and applicable national laws. We will ensure respect for people and for human dignity and fair distribution of research benefits, and will protect the values, rights and interests of our research participants.

It is important to note that the proposed research does not involve:

- research activity aimed at human cloning for reproductive purposes;
- research activity intended to modify the genetic heritage of human beings, which could make such changes heritable;
- research activity intended to create human embryos solely for the purpose of research or for the purpose of stem cell procurement, including by means of somatic cell nuclear transfer;
- research involving the use of human embryos or embryonic stem cells;
- processing of genetic information;
- animals;
- non-EU countries;

- components that will raise any environmental and health and safety concerns.

## 11.2 APPROVING EVALUATION OF THE ETHICS COMMISSION AND NOTIFICATION TO THE AUTHORITIES

The clinical trial may only be started if the approving evaluation of the ethics committee responsible for the principal coordinating investigator (PCI) and the approval of the responsible higher federal authorities have been received.

Prior to the start of the trial, notification of the start of the clinical trial is made to the responsible higher federal authorities in accordance with EU regulation No 536/2014 and national laws.

## 11.3 SUBJECT INSURANCE

On behalf of the Sponsor, the mandatory subject insurance according to national and EU regulations for all trial subjects was concluded with the following insurer:

#### 11.4 DATA PROTECTION AND CONFIDENTIALITY

The collection, transfer, storage and evaluation of personal data within this clinical trial is carried out in accordance with the applicable legal regulations (e.g. EU General Data Protection Regulation (EU reg. 2016/679 GDPR)). The prerequisite for this is the voluntary consent of the subjects in the informed consent form prior to participation in the clinical trial. During the informed consent procedure, the subjects are informed about the following:

1. data collected in the course of this clinical trial will be recorded on electronic data carriers, treated in strict confidence and only passed on to:
  - a) the sponsor of the trial (MUV) for scientific evaluation and assessment of adverse events
  - b) the responsible supervisory authorities (the regional councils or the higher federal authorities), the ethics commissions and the European database to verify the proper conduct of the trial and to evaluate trial results and adverse events.
2. To the extent necessary for the review of the clinical trial, authorized representatives of the sponsor (monitoring, auditing) and/ or the regulatory authority, who are bound to secrecy, may inspect the personal data available at the trial site. For this measure, the investigator is released from medical confidentiality.
3. Consent to the collection and processing of personal data within the scope of this clinical trial is revocable. The subject is informed that he/ she may terminate his/ her participation in the clinical trial at any time - without giving reasons and without any consecutive disadvantages. Just like the consent to participate in the clinical trial, the consent to process the collected data can be revoked at any time. According to national and EU regulations, however, in the event of revocation, the stored data may be used further to the extent necessary to
  - a) to determine the effects of the medicinal product under investigation
  - b) to ensure that the interests of the participants worthy of protection are not impaired,
  - c) to comply with the obligation to submit complete registration documents.

In the event of revocation of the declaration of consent, the responsible bodies will immediately check to what extent the stored data is still required. Data that is no longer required will be deleted immediately, unless legal and/or official documentation and reporting obligations conflict with this. However, the data processing carried out up to the point of revocation remains lawful.

#### 11.5 ETHICS AND GOVERNANCE COUNCIL

The management of this trial will be assisted and advised by an independent Ethics and Governance Council (EGC). The role of the EGC is to provide independent external supervision

and advice regarding the ethical and legal aspects of the clinical trial. The EGC will monitor the procedures in place for the clinical trial to ensure the application of the highest ethical standards, thus safeguarding patients' interests and rights. The EGC will convene regularly as an independent forum and will also be invited to take part in TSC meetings and will receive the progress and ethics reports. Questions with ethical relevance concerning the trial will also be communicated in a suitable and understandable manner for the general public on the project website, helping to inform the public debate on the new technology.

The central objectives are:

- To ensure that the study protocol and measures are in agreement with ICH-GCP and the Declaration of Helsinki.
- To ensure continuous ethical scrutiny of activities.
- To provide advice for patient consenting and inclusion regarding the randomised approach.
- To ensure – via the external EGC – independent external supervision and advice regarding the ethical, legal and safety aspects.
- To monitor the procedures in place for the study to ensure safeguard of patients' interests and entitlements.
- To review data safety measures and ensure compliance with the current EU data protection legislation.
- To provide a framework that enables trial centres to address ad hoc ethical and legal issues competently and swiftly

## 12 AMENDMENTS TO THE TRIAL PROTOCOL

In order to ensure largely comparable conditions in all trial sites and in the interest of proper data evaluation, there are no plans to change the test conditions agreed upon and laid down in the trial protocol.

In exceptional cases, however, the examination conditions may be changed. These shall only be made after mutual agreement between the investigator and the sponsor. Any change to the procedure laid down in the trial protocol must be made in writing, stating the reasons for the change, and signed by all persons responsible for the trial. The changes are then considered to be part of the protocol.

Where necessary (e.g., in the case of a change in the IMP dosing scheme or other significant changes that indicate a direct impact on the safety of the trial subjects), the consent of the ethics committees and/ or regulatory authorities responsible as well as the investigator to the protocol amendments shall be obtained, and the amendment shall be submitted to the regulatory authority.

## 13 PUBLICATION

### 13.1 FINAL REPORT

After the end of the clinical trial, the statistical evaluation is performed first and then the results report is prepared, which contains all essential results of the clinical trial. This report is submitted to the responsible higher federal authority and the ethics committee within one year after the end of the clinical trial. In addition, the results and, if necessary, other necessary information will be published in the European database.

